### Eligibility criteria

Women will be eligible to participate in the trial if they present the following:At least 36 weeks of gestation with a live fetusCephalic (head–down presentation)

Women will be ineligible to participate if they develop moderate to severe pre-eclampsia, or experience severe essential hypertension, and if they are being treated for insulin-dependent diabetes (gestational or pre-pregnant). Women will also be excluded if the fetal heart rate trace is abnormal or suspicious or if they experience an intra-uterine death.

### Randomisation and allocation concealment

Practitioners and participants will know the allocation group for the women, as the woman will either use the peanut ball or not use the peanut ball, so they will not be blinded. A computerised, internet-based central randomisation service (sealedenvelope.com) will be used to provide randomisation and allocation concealment. The research assistant and other investigators performing data collection, entry and analysis will be blind to group allocation. The women will be randomly assigned to either the control or intervention group by the random allocation selection process that will involve sealed opaque envelopes that only the midwife opens once the woman consents to be involved in the pilot study. If the woman is assigned to the intervention group, she would participate in using the peanut birthing ball, and if she is assigned to the control group, she would not use the peanut birthing ball.

### Treatment schedule

This study uses the same model (see Fig. 1) as the previously aforementioned three randomised control trials [13–15] in the USA, although Evans and Cremering (2016) only included women having their first babies and Roth et al. (2016) only included women having an elective induction (not spontaneously labouring).

**Fig. 1 Fig1:**
[figure not shown]
Participant flow peanut ball versus no peanut ball pilot randomised controlled trial.

#### Peanut ball

Women in this group will use the peanut ball during labour. The peanut ball is latex free and burst resistant. Ideally, the woman should commence using the peanut ball following insertion of the epidural, when the epidural has taken effect, so that the woman is comfortable and pain-free. It is important to change the woman’s position if she is using the peanut ball during labour with an epidural every 30 min. There are four main positions to be used with the woman having an epidural when she is using the peanut ball.*The side lying position* is when the woman is lying on her side, and the peanut ball is wedged between her legs. The top leg lays on the top of the peanut ball curve, and the bottom leg is bent underneath the peanut ball curve. The head of the bed is elevated as much as possible to ensure that the woman is comfortable—see image.
[figure not shown]
*The tuck position* is also a side lying position, and the legs are pulled up towards the woman’s head and the ball is brought forward towards the woman’s chest so that the woman can hug the ball with her arms. The head of the bed should also be elevated as much as possible to ensure that the woman is comfortable. This position can also be used for pushing—see image.
[figure not shown]
*The semi sitting position* is when the woman is sitting semi recumbent, and the top leg rests over the peanut ball over the natural curve and the bottom leg is bent and rests under the ball—see image.
[figure not shown]
*The Taylor position* is similar to the semi sitting position, although the legs squeeze the ball and the bottom leg moves up a bit higher towards the woman’s head—see image.
[figure not shown]

#### Not using peanut ball

The group of women not using the peanut ball will be provided the usual care during labour if using an epidural for pain relief.

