### Measures used to achieve objectives

#### Primary objectives

*Willingness of women to be randomised into the control or intervention group*
The measure used to assess this objective will be assessed by the midwife in the birthing unit, and once the woman has an epidural in situ, the woman will then be consented by the midwife. The midwife will then access the sealed opaque envelopes that allocate the woman to the group using the peanut ball or the group receiving standard care and not using the peanut ball (this has been generated by the computer software: sealedenvelope.com). The midwife will have no previous knowledge of which group the woman will be allocated to until the envelope is opened (allocation concealment). If the woman has been allocated to the group not using the peanut ball and she decides she wants to use the peanut ball, the woman’s reasons for using the peanut ball will be noted and the midwife will notate this in the Peanut Ball Research Notebook that accompanies the boxes for information and consent and the allocation box in the birthing suite. The Coordinating Investigator will liaise and visit contacts at both sites for this information.
*Estimation of recruitment and attrition rate*
Acceptability of the recruitment methods will be assessed including any adverse events recorded whilst using the peanut ball during labour (these details will be accessed via the Electronic Medical Record or woman’s progress notes during labour by the coordinating investigator). The main method of recruitment of the women will be midwives working in the birthing unit, identifying and approaching the woman, as they have been previously educated about the research project by education sessions and an education package has also been written for the midwives about using the peanut ball for the research project provided by the coordinating investigator. Sample size analysis should be adequate to estimate the recruitment rate [18]. Modifications may be made to the protocol for the full trial based on recruitment rates.
*Estimation of women staying in allocated group*

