Midwives will record in the Peanut Ball Research Notebook in the birthing unit if the woman changes her mind if she is allocated to the control or intervention group and decides to change to the other group other than the group she has been allocated. It is important to achieve an “intention to treat analysis” and that participants are analysed according to the group they are originally allocated [19].
*To determine why women stopped using the peanut ball*
The Coordinating Investigator will access the Electronic Medical Record to assess why the woman stopped using the peanut ball. It is important to achieve an “intention to treat analysis” to determine whether or not they adhered to or accepted the intervention. The importance of reporting of numbers and the reasons why participants were lost to follow up is necessary to assess the extent to what the intention to treat may lead to and provide an underestimate of the efficacy of the intervention under ideal circumstances [19].
*To assess likely primary and secondary outcome measures to inform sampling size and powering of the definitive RCT*
The main purpose of this pilot study is to assess the feasibility of conducting a full definitive trial and not to generate statistically significant results. Nonetheless, a secondary aim is to inform the sample size calculation to design a full definitive trial. This requires an estimate of a clinically meaningful effect size and variance that can be entered into a sample size calculation. The key primary clinical outcome is the rate of vaginal births, and the key secondary outcome is the length of labour. For this pilot study, a decision was taken to opt for 50 pregnant women (25 in each trial arm) to inform this process. Indeed, a previous pilot study that investigated the use of the peanut ball with similar aims determined that this sample size may actually be sufficient to demonstrate statistically significant findings [13]. Therefore, given the high feasibility of recruiting these numbers of women at the study sites, a decision was then made to aim for 50 pregnant women in total (as a minimum), and so opt for a comprehensive pilot trial to ensure the pilot can confidently test feasibility and also inform the powering of a future definitive trial.

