## Discussion

The peanut ball is a non-pharmacological method of pain relief that may be used by women using epidurals in labour, and preliminary randomised controlled trials in the USA have shown clinically and statistically significant findings. Currently, peanut balls are being used by women during labour, in hospitals in Australia; however, there is no existing evidence that the peanut ball makes a difference for women, either as a birthing ball or whilst using an epidural. It is important to fully investigate the potential benefits of using the peanut ball in Australia, especially when we are now working with increased rates of caesarean sections [23].

The web-based survey about the woman’s general health will provide general physical and mental health information about mobility, self-care, usual activities, pain, discomfort, anxiety and depression. We would expect that this cohort of pregnant women with low-risk pregnancies will provide a result of a generally healthy population. The web-based survey about using the peanut ball will provide a snapshot of information about the woman’s level of satisfaction, positions she used, her perception about influencing the length of labour, level of empowerment and whether she would recommend the peanut ball to other women using epidurals during labour. Demographics will also be collected. Expected results in the overall context of the study would show that the peanut ball has benefits for women using epidurals in labour, not only in her positive perception and feeling of empowerment but also increasing her comfort.

This study will be the first to investigate the pilot effect of the peanut ball for women using epidurals in labour in a low-risk maternity model of care in Australia. It is expected that the mean clinical and health service outcomes will improve in the peanut ball arm. If the results point to reject using the peanut ball and no benefits are found, it is expected that midwives will continue to suggest using the peanut ball to increase comfort and empowerment for women using epidurals in labour. The pilot trial will inform the development of a fully powered definitive trial to assess the clinical meaningful and statistically significant outcomes, including an economic evaluation to assess cost effectiveness.

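### Adherence to allocation is a primary objective, but a departure is logged only when the woman changes her mind, so ball use or non-use that starts otherwise may not be counted

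*Protocol article*

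**What the plan says.** The Objectives section of the protocol article lists the number of women staying in the allocated group among the primary objectives.

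The control arm is described three times. Under Randomisation and allocation concealment: "if she is assigned to the control group, she would not use the peanut birthing ball". The section headed Not using peanut ball states: "The group of women not using the peanut ball will be provided the usual care during labour if using an epidural for pain relief". Under Measures used to achieve objectives, the comparator is "the group receiving standard care and not using the peanut ball".

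The measure of adherence is also set out under Measures used to achieve objectives, in two places. For the willingness objective, the midwife makes a notebook entry in this case: "If the woman has been allocated to the group not using the peanut ball and she decides she wants to use the peanut ball". For the objective on staying in the allocated group, midwives make an entry "if the woman changes her mind if she is allocated to the control or intervention group and decides to change to the other group".

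The Quantitative data part of Statistical analysis then takes willingness, recruitment, attrition and adherence from that notebook. The electronic medical record is named for adverse events during ball use, for women lost to follow-up, and for whether and why women stopped using the ball.

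**The concern.** Adherence is a matter of what each woman received. The stated rule records something narrower: a decision by the woman to leave her group. The two can differ in both arms. A control woman may be placed on the ball at a midwife's suggestion, and an intervention woman may never have the ball placed although she has not changed her mind. Read literally, neither event calls for an entry.

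The result feeds a primary feasibility conclusion. The investigators must judge from this pilot whether the two arms can be kept apart in a definitive trial in which staff and women know the allocation. An adherence figure that can err in only one direction, towards looking better, is a weak basis for that judgement. It also leaves the clinical difference between arms harder to interpret, because the extent of crossover behind it is not known.

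**Working it through.** The plan gives no expected adherence or crossover rate, so there is no figure of its own to reproduce. The check is a comparison of the stated rules, followed by simple arithmetic for scale.

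**1. What is to be estimated.** The number of women staying in the allocated group (Objectives, primary).

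**2. What triggers a record.** Both descriptions under Measures used to achieve objectives make the woman the one who decides. Neither refers to ball use as such, or to use or non-use that someone else initiates.

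**3. Where the estimate comes from.** The notebook only (Quantitative data).

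**4. Whether another named source fills the gap.**
- The medical record is to be searched for stopping the ball. That covers an intervention woman who started and then stopped. It does not cover one who never started, or a control woman who started.
- The medical record or progress notes are to be searched for adverse events while using the ball. That would reveal control use only if an event occurred.
- Maternal position in labour is collected, but it is not described as a record of ball use.
- The Setting section has women recontacted for an online survey if they used the ball. Actual use therefore has to be known for another purpose, but it is not linked to the adherence measure.

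**5. Whether the midwife's route is plausible.** The Background describes midwives as autonomous and as promoting non-drug methods, and mentions their suggesting the ball to women with epidurals. Birthing-unit midwives are educated in its use for the study. The Discussion adds "Currently, peanut balls are being used by women during labour, in hospitals in Australia". This makes the route plausible. It does not show that it occurs at the two sites.

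**6. Scale.** Take n = 25 per arm (the planned minimum), d true departures and u of them unlogged.
- True adherence = (25 − d)/25. Reported adherence = (25 − d + u)/25. Overstatement = u/25.
- u = 1 gives 4 percentage points, u = 3 gives 12, and u = 5 gives 20. These values of u are assumptions.
- If no departure is logged in 25 women, the exact 95% upper limit for the departure proportion is 1 − 0.025^(1/25) = 13.7%.
- If five women had in fact departed, the estimate would be 5/25 = 20% (exact 95% interval 6.8% to 40.7%). The interval reported from a notebook with no entries, 0 to 13.7%, would then exclude the proportion that actually occurred in the sample.

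With complete recording, 25 women per arm already give only a rough estimate. Incomplete recording adds a bias that the interval does not show.

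**The case against.** **Accepting an offer is a decision.** A control woman who takes a ball offered by the midwife can be said to have decided to change group, and the midwife is the one who writes the entry. This stands in part, and it is why the use may, rather than will, go uncounted. It also means that midwives at two sites could treat the same event differently, which is a reason to define it.

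**The article condenses a fuller protocol.** The full protocol is an additional file that is not shown, and the notebook may already have fields for actual use. That is possible, and the absence of such fields from the article is not the point. The point is the trigger, which the article does state, twice, after saying that the measures are detailed for each objective.

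**Stronger readings that the document does not support.**
- A reader might infer that the control arm is contradictory, with no ball in one place and usual care, which might include the ball, in another. The usual-care sentence stands under the heading Not using peanut ball and concerns women not using it, and the Measures section joins the two conditions. No part of the article allows the ball as control care.
- A reader might take the Discussion's "it is expected that midwives will continue to suggest using the peanut ball" as evidence that controls will be offered the ball. That sentence is conditional on a finding of no benefit and concerns practice after the results. The remark on current use concerns Australian hospitals in general and does not name the trial sites.
- A reader might conclude that the definitive trial would be undersized by a calculable factor. No contamination rate is given. If the pilot's as-allocated difference were the planning input and crossover were similar later, that difference would already include the dilution.

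**Conclusion.** The point holds in a limited form. The rule stated for a primary objective records the woman's change of mind, not use or non-use of the ball, and the adherence figure is drawn from that record. Adherence may therefore be overstated in either arm, by 4 percentage points for each missed woman at 25 per arm. How many would be missed cannot be derived from the document. The conclusion assumes that midwives follow the written trigger literally and that no form outside the article records actual use. The description of the control arm needs no correction, and no sample-size consequence can be quantified. This is a defect of measurement definition. It is worth correcting because a primary feasibility estimate depends on it and because unrecorded use may be hard to recover afterwards. The article states that recruitment has not commenced.

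**What to change.** In Measures used to achieve objectives, under the objective on women staying in the allocated group, define a departure from allocation by actual ball use: any use in a woman allocated to control, or no use in a woman allocated to the ball, whoever initiated it. Align the entry described under the willingness objective and the data source named under Quantitative data with this definition.

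In the notebook, record for every randomised woman in both arms, and not only for those who switch:
- whether the ball was used;
- who initiated its use;
- when it was started and stopped.

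Keep the reason for a change of mind as a separate item, since it serves the willingness objective. Report the departure proportion by arm with an exact confidence interval, and keep every woman in her allocated arm for the clinical outcomes, as the article already intends.

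The cost is one short record for each of about 50 women, a small change of wording, and possibly a less favourable adherence figure. If the full protocol's forms already capture actual use, only the definition and the named source need to change.

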### Objectives

The study will have a number of pre-specified measures to address the following objectives, and these measures are detailed for each objective. The primary objectives (see Table 1) relate to progressing the trial to a definitive RCT trial. The secondary objectives (see Table 1) will detail the completion of the survey tools and collection of other variables that are key clinical outcomes when assessing the differences [17] between women using the peanut ball and the group who does not.

**Table 1 Tab1:** Participant timeline of assessments and interventions

	Study period									
	Enrolment	Allocation	Primip/multip	Other pain relief	Aug/induce	Apgars	Perineum	Position of woman	Cervical dilation at time of epidural insertion	Complete surveys
										Length of stay
Timepoint	During labour	During labour								Postnatal
Enrolment										
Eligibility screen Informed consent	X									
Allocation	X	X								
Interventions										
Intervention		X or								
Comparator group		X								
Assessments										
Primary objectives		X								
Secondary objectives		X	X	X	X	X	X	X	X	X

#### Primary objectives

The primary objectives of the trial include the following:To determine how many women are willing to be randomised into either the control or intervention groupTo estimate recruitment and attrition rate of women into the studyTo estimate the number of women staying in the allocated groupTo determine why women stopped using the peanut ballTo assess likely primary and secondary outcome measures to inform sampling size and powering of the definitive RCT

#### Secondary objectives

The secondary objectives include the following:To investigate completion of the health and satisfaction surveysTo assess the feasibility of conducting an economic evaluation alongside a future definitive trialTo measure key clinical outcomes and differences between the control and intervention group (see Table 1)

Table 1 outlines the participant timeline of assessments and interventions.

### Measures used to achieve objectives

#### Primary objectives

*Willingness of women to be randomised into the control or intervention group*
The measure used to assess this objective will be assessed by the midwife in the birthing unit, and once the woman has an epidural in situ, the woman will then be consented by the midwife. The midwife will then access the sealed opaque envelopes that allocate the woman to the group using the peanut ball or the group receiving standard care and not using the peanut ball (this has been generated by the computer software: sealedenvelope.com). The midwife will have no previous knowledge of which group the woman will be allocated to until the envelope is opened (allocation concealment). If the woman has been allocated to the group not using the peanut ball and she decides she wants to use the peanut ball, the woman’s reasons for using the peanut ball will be noted and the midwife will notate this in the Peanut Ball Research Notebook that accompanies the boxes for information and consent and the allocation box in the birthing suite. The Coordinating Investigator will liaise and visit contacts at both sites for this information.
*Estimation of recruitment and attrition rate*
Acceptability of the recruitment methods will be assessed including any adverse events recorded whilst using the peanut ball during labour (these details will be accessed via the Electronic Medical Record or woman’s progress notes during labour by the coordinating investigator). The main method of recruitment of the women will be midwives working in the birthing unit, identifying and approaching the woman, as they have been previously educated about the research project by education sessions and an education package has also been written for the midwives about using the peanut ball for the research project provided by the coordinating investigator. Sample size analysis should be adequate to estimate the recruitment rate [18]. Modifications may be made to the protocol for the full trial based on recruitment rates.
*Estimation of women staying in allocated group*
Midwives will record in the Peanut Ball Research Notebook in the birthing unit if the woman changes her mind if she is allocated to the control or intervention group and decides to change to the other group other than the group she has been allocated. It is important to achieve an “intention to treat analysis” and that participants are analysed according to the group they are originally allocated [19].
*To determine why women stopped using the peanut ball*
The Coordinating Investigator will access the Electronic Medical Record to assess why the woman stopped using the peanut ball. It is important to achieve an “intention to treat analysis” to determine whether or not they adhered to or accepted the intervention. The importance of reporting of numbers and the reasons why participants were lost to follow up is necessary to assess the extent to what the intention to treat may lead to and provide an underestimate of the efficacy of the intervention under ideal circumstances [19].
*To assess likely primary and secondary outcome measures to inform sampling size and powering of the definitive RCT*
The main purpose of this pilot study is to assess the feasibility of conducting a full definitive trial and not to generate statistically significant results. Nonetheless, a secondary aim is to inform the sample size calculation to design a full definitive trial. This requires an estimate of a clinically meaningful effect size and variance that can be entered into a sample size calculation. The key primary clinical outcome is the rate of vaginal births, and the key secondary outcome is the length of labour. For this pilot study, a decision was taken to opt for 50 pregnant women (25 in each trial arm) to inform this process. Indeed, a previous pilot study that investigated the use of the peanut ball with similar aims determined that this sample size may actually be sufficient to demonstrate statistically significant findings [13]. Therefore, given the high feasibility of recruiting these numbers of women at the study sites, a decision was then made to aim for 50 pregnant women in total (as a minimum), and so opt for a comprehensive pilot trial to ensure the pilot can confidently test feasibility and also inform the powering of a future definitive trial.

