Both surveys will be distributed to the respondents from an electronic platform—Qualtrics [21] platform—and have been electronically tested to assess the functionality prior to distribution of the online survey. Each survey will be distributed to the participant’s email and de-identified in the computer database. All surveys will be analysed, including those not completed. All of the data collected in this closed survey will be stored in a password-protected computer and will only be accessible by the researchers.
*To assess the feasibility of conducting an economic evaluation alongside a future definitive trial*
The feasibility of collecting data required for an economic evaluation will be tested. For this pilot, we will collect information on health service usage between trial arms, including staff time, medications, procedures and length of stay in hospital. The inclusion of the EQ5D5L will assess the feasibility of incorporating an economic measure of HRQoL, where responses will be converted into ‘health utilities’.
*To measure key clinical outcomes and differences between the control and intervention group*
Details about other birth outcomes will also be collected to determine the baby’s condition, perineal damage, other methods of pain relief used, position of mother and baby during labour, blood loss, cervical dilatation at time of insertion of epidural and evidence of augmentation and/or induction of labour.

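### The adverse-event collection the article describes follows peanut-ball use rather than randomised arm, so events outside the named outcomes have no control count and no window after use

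*Protocol article*

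**What the plan says.** Under Measures used to achieve objectives, Primary objectives, the item on estimating recruitment and attrition contains the article's only description of adverse-event collection: "Acceptability of the recruitment methods will be assessed including any adverse events recorded whilst using the peanut ball during labour". On the source it adds that "these details will be accessed via the Electronic Medical Record or woman’s progress notes during labour by the coordinating investigator".

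The next item, on women staying in their group, expects some women to change group, has midwives note this in a notebook, and asks for intention to treat, so that "participants are analysed according to the group they are originally allocated [19" is the rule.

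Other text bears on harm without using the term. One secondary objective is "To measure key clinical outcomes and differences between the control and intervention group". Under it, "Details about other birth outcomes will also be collected to determine the baby’s condition, perineal damage, other methods of pain relief used", and the same sentence goes on to blood loss. Table 1 lists Apgars, perineum and length of stay. The Statistical analysis section compares vaginal birth rate and length of labour. For the economic objective, "we will collect information on health service usage between trial arms, including staff time, medications, procedures and length of stay in hospital". Neither the objectives nor Table 1 has an entry for adverse events or safety.

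**The concern.** A count of adverse events can be read against the randomised design only if it is taken in the same way in both arms. Women labouring with an epidural can have recordable events whether or not they use a ball. A count that begins and ends with ball use cannot separate the ball from that background. It also leaves out a problem noted after the ball is removed, unless the problem happens to be one of the named outcomes.

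The article expects crossover and provides for recording it, so exposure and allocation will differ for some women. For adverse events the collection rule follows the first and the analysis rule the second. What is at stake is how the pilot's adverse-event record can be used when the definitive trial is designed: a few events in the ball group would have no comparator, and an absence of late events could simply reflect where collection stopped. Placing the item under recruitment acceptability also makes it likely to be overlooked in reporting, because adverse events do not measure recruitment.

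**Working it through.** The article gives no adverse-event rate or safety figure to reproduce. Its one relevant number is the sample size, "a decision was taken to opt for 50 pregnant women (25 in each trial arm) to inform this process"; 2 × 25 = 50 agrees.

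**Step 1: who is counted under the wording as it stands (events outside the named outcomes).**

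- Control, never uses the ball: not counted.
- Control who crosses over: counted while using the ball.
- Ball arm, using the ball: counted while using it.
- Ball arm, stopped: not counted from then on.
- Ball arm, never started: not counted.

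Let *a* be the number of ball-arm women who never use the ball and *c* the number of controls who cross over. The women observed number (25 − *a*) from the ball arm and *c* from the control arm. With full adherence (*a* = *c* = 0) that is 25 against 0, and no difference by arm can be estimated. With any crossover, the few controls observed are those who were exposed.

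**Step 2: size of the uncompared background.** The event rate is not in the documents. Assume 10% of women with an epidural have some recordable event, with a range of 5% to 20%. Expected events in the ball arm are then 25 × 0.10 = 2.5 (25 × 0.05 = 1.25 to 25 × 0.20 = 5). Under this assumption, about one to five events would arise with no control count beside them, even if the ball had no effect.

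**Step 3: what symmetric collection would give.**

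- Upper limit after 0/25: two-sided 95%, 1 − 0.025^(1/25) = 13.7%; one-sided 95%, 1 − 0.05^(1/25) = 11.3%.
- Chance of at least one event in an arm, 1 − (1 − p)^25: 22% at p = 1%, 40% at 2%, 72% at 5%, 93% at 10%.
- Power at 25 per arm, two-sided 0.05, assumed rates: 10% for 5% v 10%; 16% for 10% v 20%; 36% for 5% v 20%; 65% for 5% v 30%.
- Fisher's exact test against 0/25: 5/25 gives p = 0.0502 and 6/25 gives p = 0.022, so six events are needed.

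Step 3 shows the limit of the remedy. Collecting in both arms supplies the missing comparator but does not make 25 per arm informative about anything except large differences. The 13.7% comes from the sample size and is the same with or without the change.

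**The case against.** The strongest reply is that this is a journal article. It points to a full protocol, designed in accordance with SPIRIT, as an additional file that is not shown here, and that file may hold wider adverse-event procedures. The sentence in question lists what feeds an acceptability measure; it does not say that events are recorded nowhere else. This stands as a limit, so the point is confined to the only collection the article describes. It does not remove the point, because the article states a rule instead of leaving the matter open, and the rule restricts by exposure and by time.

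A reader might infer that the pilot has no control comparison of harm at all. The documents do not support that: baby's condition, Apgars, perineal damage, blood loss, birth mode, length of labour and procedures are planned for both arms. Nor do they support the inference that all later harm is missed. Several of these items, and length of stay, are observed at or after birth. The Background also says that all women are surveyed on general health, although the consent section mentions recontact only for ball users. What remains uncovered is events outside those lists.

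It can also be said that intention to treat governs analysis, and that recording events during exposure is legitimate for describing a device. That is fair, and it is a reason to keep a flag for events during use. But events never collected in controls, or after use, cannot later be analysed by allocated arm.

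**Conclusion.** The point holds in a limited form. In the article as written, adverse-event collection follows ball use. For events beyond the birth outcomes and health-service items already planned, there is no control-arm count (0 of 25 women, crossovers aside) and no capture after use. This is inconsistent with analysis by allocated group, and the item is filed under the wrong measure.

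It would be tempting to conclude that the wording leaves the pilot unable to judge safety. That goes too far: safety is not a listed objective, the article disclaims power for meaningful tests, and 25 per arm could not settle the question even with symmetric collection. The gain from a change is less ascertainment bias in a descriptive table.

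The conclusion rests on reading the sentence literally and on the full protocol not already providing for both arms. The figure of 1.25 to 5 background events rests on an assumed event rate of 5% to 20%.

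**What to change.** Reword the adverse-event sentence in the primary-objective measures along these lines: adverse events will be extracted from the medical record on the same form in both arms, from opening of the allocation envelope to hospital discharge, and reported descriptively by allocated arm as counts with exact confidence intervals, with a flag for events that occurred during ball use. Move this out of the recruitment and attrition measure and list it as a separate item in Table 1. If the full protocol already says this, bring the article's sentence into line with it.

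The cost is about 25 additional chart reviews (the control arm) and a longer window for every woman. The source is routine, the coordinating investigator is already to read it, and recruitment had not begun when the article was written. Because the flag reveals ball use and the article wants data collectors blind to group, it is best completed after the events have been listed. The report should state that the comparison is descriptive and that zero events in 25 is compatible with a true rate of up to 13.7%.
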